##### Computational modeling

MATLAB 2019a (https://www.mathworks.com/) and the Reinforcement Learning algorithm will be used to model the behavioral data and estimate the learning rate α, inverse temperature parameter β, repetition parameter p, and model-based learning weight ω of individual subjects.

① value estimates. The state-action values for the first and second stages of each trial are determined by the weighted sum of the model-based action value Q_MB_ and the model-free action value Q_MF._ The weighted sum is expressed as follows.

(1)
$$\begin{array}{l} Q_{net}\left(S_{A},a_{j}\right)=\omega Q_{MB}\left(S_{A},a_{j}\right)+{\left(1-\omega \right)Q}_{MF}\left(S_{A},a_{j}\right) \end{array}$$

It is assumed that individual behavioral choice in the first stage is the weighted sum of goal-directed and habitual learning, with the weight of ω (0~1). If ω is close to 0, the choice mainly depends on habitual learning; if ω is close to 1, the choice mainly depends on goal-directed learning.

(a) Model-based state-action value:

(2)
$$\begin{array}{l} Q_{MB}(S_{A},a_{j})=P(S_{B}|S_{A},a_{j})\underset{a\in \{a_{A},a_{B}\}}{\max}Q_{MF}(S_{B},a)\\ \;+P(S_{C}|S_{A},a_{j})\underset{a\in \{a_{A},a_{B}\}}{\max}Q_{MF}(S_{C},a) \end{array}$$

(b) Model-free state-action value:

(3)
$$\begin{array}{l} Q_{MF}\left(S_{i,t},a_{i,t}\right)=Q_{MF}\left(S_{i,t},a_{i,t}\right)+\alpha_{i}\delta_{i,t} \end{array}$$

For the first and second stages, learning rates α_1_ and α_2_, respectively, represent the extent to which the reward results are used for learning.

(c) Prediction error:

(4)
$$\begin{array}{l} \delta_{i,t}=r_{i,t}+Q_{MF}\left(S_{i+1,t},a_{i+1,t}\right)-Q_{MF}\left(S_{i,t},a_{i,t}\right) \end{array}$$

The action probabilities of the first and second stages of each trial are regarded as a softmax function of the inverse temperature parameter β, the repetition parameter *rep*, and the indicator function *p* as follows.

(5)
$$\begin{array}{l} P(a_{i,t}=a|s_{i,t})=\frac{exp(\beta [Q_{net}(s_{i,t},a)+p\cdot rep(a)])}{\sum_{a^{\prime }}exp(\beta_{i}[Q_{net}(s_{i,t},a^{\prime })+p\cdot rep(a^{\prime })])} \end{array}$$

The inverse temperature parameters β_1_ and β_2_ represent the randomness of the first- and second-stage choices. The repetition parameter p and the indicator function represent the reproducibility of the choice, that is, the tendency to choose the same choice as in the previous trial, regardless of the actual value of the choice. Additionally, *p* > 0 represents choices the same as the previous trial, and *p* < 0 represents choices different from the previous trial.

The parameters of each subject will be estimated using the R software and its Stan toolkit with the Markov Chain Monte Carlo (MCMC) estimation which has been previously described (4). The model evidence of the Akaike information criterion (AIC) and the Bayesian information criterion (BIC) will be calculated separately to estimate the model fit of reinforcement learning to the behavior.

#### Imaging data

##### Preprocessing analysis

DPABI V7.0 software (http://rfmri.org/DPABIV7) will be used for data pre-processing, in which the DICOM data will be converted into NIFTI format. In order to remove the effects of subject maladaptation during the scan as well as the effects of inhomogeneous magnetic fields on the results, data from the first 10 time points will be removed. Then, time correction, head motion correction, image standardization, image smoothing, detrending, and filtering (0.01~0.08 Hz) will be conducted, as well as the removal of head motion parameters.

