##### Real-time magnetic resonance imaging

MR images will be collected using 3.0T Siemens (Trio, Erlangen, Germany) with a 32-channel head coil. T1-weighted structural images will be collected from the whole brain with the magnetization-prepared rapid gradient echo (MPRAGE) sequence for anatomical localization of functional images. FOV = 256 × 256 mm, 176 sagittal slices, layer thickness = 1.0 mm, resolution = 1.0 mm^2^, TR/TE = 1900/2.52 ms, and flip angle = 9°. Echo-planar imaging (EPI) T2^*^-weighted functional images will be collected across the whole brain using a gradient echo planar imaging (EPI) sequence, FOV = 192 × 192 mm, matrix size = 64 × 64, and spatial resolution = 3 × 3 × 3 mm^3^, flip angle = 90°, and TR/TE = 2000/30 ms. To reduce the head motion, a strip of medical tape will be attached horizontally over the forehead of the participant and be spread to both sides of the head coil so that the participant could feel the head motion subjectively to prevent it from exceeding the range of head motion (39).

Real-time functional imaging will be achieved by using a customized function during MR image reconstruction, with TurboExport (Brain Innovation, Maastricht, The Netherlands) to convert input pixel data for each volume into images. Each image generated will be preprocessed in real time using the Turbo-BrainVoyager (Brain Innovation, Maastricht, The Netherlands). Preprocessing includes motion correction (by realigning each image to the first image of the session) and spatial smoothing (Gaussian kernel of half-height and 5 mm in full width). The computer presenting the task will communicate with Turbo-BrainVoyager via Transmission Control Protocol (TCP) to acquire preprocessed real-time data to be coregistered to the localizer anatomical image (first session) and generate feedback displays to the participants.

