##### Task-state PE signal analysis

BOLD signal analysis of ROIs during the task will be performed using SPM12 (https://www.fil.ion.ucl.ac.uk/spm/software/spm12/). The PE and relative partial differential calculations in the action selection phase and the reward outcome phase will be included as regressors in the general linear model, with ω (see Equation 1) as a covariate (30). The standard hemodynamic function will be constructed for ROIs using MarsBaR (https://sourceforge.net/projects/marsbar/) with FDR correction for control of false discovery rate in voxelwise tests (41). The ROIs will be made with WFU_PickAtlas software (https://www.nitrc.org/projects/wfu_pickatlas) according to the activation map during MDT for PEs.

The ROIs within CEN/SN will be mapped to CEN and SN which are functionally defined according to 14 intrinsic connectivity networks (ICNs) that are comprised of 90 distinct ROIs (42, 43). The DMN, SN, and CEN will be constructed from network templates with the Group ICA of fMRI Toolbox (GIFT, http://mialab.mrn.org/software/gift/) for use in the constrained ICA. The differential functional image (CEN - SN strength) during the first session will be used to create individualized network masks as neurofeedback target regions during the subsequent sessions. The nuisance regressors including six motion parameters and temporal derivatives as well as their quadratic terms and 25 physiological noise components will be taken into consideration. The first two runs of the first session will be discarded without additional analysis. The time courses (extracted using Turbo-BrainVoyager online) of ROIs will be high-pass filtered (0.01 Hz/100 s) and normalized (z-transformed).

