##### Self-regulation performance

For each subject in the patient group in each session, self-regulation performance will be assessed with the CEN-SN activation difference (computed through online time courses of ROIs extracted using Turbo-BrainVoyager) during the training. Self-regulation performance will be defined as the mean % signal change of ROIs (CEN and SN) over all the NF runs. The self-regulation performance will then be submitted to an ANOVA with the factors group (NF vs. YC) and session (four sessions) for the group and/or time effects of rt-fMRI NF training.

Additionally, to investigate the pre- and post-training difference in CEN-SN functional connectivity for each patient group, we will apply the paired *t*-tests or Wilcoxon signed-rank tests (depending on parametric or non-parametric distributions) between the pre- and post-training tests, while undergoing MDT behavioral task during neuroimaging.

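### As written, the 0.01-0.08 Hz band-pass reaches the event-related prediction-error model, where it removes part of the signal and makes single-subject standard errors too small

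*Protocol article*

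**What the plan says.** Under Imaging data, the Preprocessing analysis section describes one DPABI chain that "will be used for data pre-processing, in which the DICOM data will be converted into NIFTI format". Among its later steps, "detrending, and filtering (0.01~0.08 Hz) will be conducted". No analysis is named as the one this filter serves, and the methods describe no resting-state scan.

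The next section, Task-state PE signal analysis, states that "BOLD signal analysis of ROIs during the task will be performed using SPM12". For that model, "The PE and relative partial differential calculations in the action selection phase and the reward outcome phase will be included as regressors". The same section mentions voxelwise tests with FDR control and takes ROIs from the PE activation map of the task. CEN-SN functional connectivity (Self-regulation performance) also comes from the task scan, acquired "while undergoing MDT behavioral task during neuroimaging".

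Only one other filter is stated. It concerns the ROI time courses extracted online during neurofeedback, which "will be high-pass filtered (0.01 Hz/100 s) and normalized (z-transformed".

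**The concern.** PE regressors change from trial to trial at two phases of each trial, so part of their variance lies above 0.08 Hz. A low-pass there has two effects on a GLM fitted afterwards.

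- It discards that part of the signal. If the design is not filtered in the same way, the fitted PE betas shrink. The article does not say that the design is filtered.
- It removes most of the high-frequency noise and leaves smooth, strongly autocorrelated residuals. The usual residual variance and degrees of freedom then make single-subject standard errors too small.

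At stake is any single-subject PE map used for inference or to choose ROIs, and the size of the PE betas carried to group level.

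**Working it through.** The article gives no figure on this point to reproduce.

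**Inputs from the article.** Pass band 0.01-0.08 Hz (Preprocessing analysis). Functional sequence "flip angle = 90°, and TR/TE = 2000/30 ms" (Real-time magnetic resonance imaging), the only one described and so taken to apply to the task scan. PE terms at two phases (Task-state PE signal analysis).

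**Assumptions.** The text gives no trial timing or length of the task run. Assumed: jittered trial spacing of 6-16 s, runs of 600 or 1200 s, AR(1) noise with coefficient 0.3, and a double-gamma haemodynamic response. The version with both phases modelled uses spacing of 8-14 s and phases 2.5 or 4 s apart.

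**Step 1: share of the spectrum kept.** Nyquist frequency = 1/(2 × 2 s) = 0.25 Hz.
- Band-pass: (0.08 − 0.01)/0.25 = 0.28.
- 0.01 Hz high-pass alone: (0.25 − 0.01)/0.25 = 0.96.

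The band-pass therefore gives up about 72% of the nominal temporal degrees of freedom.

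**Step 2: PE signal.** In simulation, the 0.08 Hz cut keeps 0.86-0.89 of the PE variance left after the high-pass, a loss of 11-14%. With both phases modelled, 0.84-0.86 of the unique PE information remains, a loss of 14-16%.

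If the design is unfiltered, the fitted beta as a fraction of the true beta is close to (share kept by the high-pass) × (share kept by the low-pass):
- 600 s run, 6 s spacing: 0.966 × 0.865 = 0.836 (simulated 0.835).
- 1200 s run, 16 s spacing: 0.921 × 0.869 = 0.800 (simulated 0.800).

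Across all settings the fraction is 0.80-0.84. The high-pass alone accounts for about 3-8% of PE variance.

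**Step 3: single-subject standard errors.** An approximation with white noise of variance σ², 0.84 of PE variance kept, and an unfiltered design fitted by ordinary least squares (OLS):
- reported variance of beta ≈ 0.28σ²/x′x
- true variance of beta ≈ 0.84σ²/x′x
- reported SE / true SE = √(0.28/0.84) = 0.58
- rejection rate at nominal 5% = 2·P(Z > 1.96 × 0.58) ≈ 0.26

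Simulation with AR(1) noise gives an SE ratio of 0.59-0.60. First-level type I error at nominal 5%:

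| Data | Design | Fit | Type I error |
|---|---|---|---|
| 0.01-0.08 Hz | unfiltered | OLS | 24-27% |
| 0.01-0.08 Hz | unfiltered | AR(1) prewhitened | 20-23% |
| 0.01-0.08 Hz | same filter, degrees of freedom uncorrected | OLS | 30-32% |
| 0.01 Hz high-pass | same high-pass | AR(1) prewhitened | 6-7% |

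The residual lag-1 correlation after the band-pass is about 0.83. AR(1) prewhitening does not repair the error rate.

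**Step 4: group level.** A one-sample t test on 20 subject betas from band-passed null data (600 s run, 10 s spacing) rejects 4.7% of the time. The second-level test takes its error from the spread between subjects, so it keeps its level.

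**The case against.** The strongest reply is that no sentence says the band-passed data enter the PE GLM. Connectivity is one of the offline analyses and is a natural use for such a band. The PE section also lists a fuller nuisance set than the preprocessing section, so there may be more than one chain. The article is condensed and refers to a preregistration that is not shown. This stands in part: reach to the task GLM is inferred from a single unrestricted chain and the absence of any other offline scan. If connectivity alone was meant, the text does not say so, and an analyst following it would low-pass the task data.

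Three stronger readings are tempting and are not supported.

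- *That the filter removes the PE signal.* Most of it survives. Beta shrinkage also overstates the loss of sensitivity, because noise is removed too. With white noise, the true signal-to-noise ratio changes by 0.84/√0.84 = 0.92, a loss of about 8%.
- *That imaging inference as a whole is invalid.* The inflation is confined to single-subject tests. The article does not say whether its voxelwise tests, or the map used to choose ROIs, are single-subject or group. The individualised neurofeedback masks come from the CEN-SN difference image of the first session, not from a PE t map.
- *That the high-pass on the online time courses contradicts the band-pass.* Those series are a separate data stream, used for self-regulation performance. Different filters for different streams are not an inconsistency.

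**Conclusion.** The point holds in limited form. The article states a filter without limiting its scope, and taken literally it low-passes event-related data before a GLM.

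The 28% figure follows from the article's own TR and band. The PE loss, the beta attenuation, the understated standard errors and the first-level error rates rest on assumed timing and noise. The error rates and beta attenuation varied little over trial spacing of 6-16 s and runs of 600-1200 s. The understated single-subject error is the larger effect, at roughly four to six times the nominal rate; the loss of PE signal is modest.

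Any single-subject PE map used for inference or ROI choice would be affected. Group tests on subject betas would keep their type I error but work with attenuated betas. HAMD-17, SHAPS, ω and the online self-regulation measure do not pass through this filter.

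**What to change.** In Preprocessing analysis, state two branches.

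1. For the MDT prediction-error GLM: a 0.01 Hz high-pass only, applied to both data and design, with SPM's autocorrelation model.
2. For the CEN-SN connectivity analysis: 0.01-0.08 Hz filtering, stated to apply to that analysis alone.

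Under the same assumptions, the first branch brings first-level type I error to 6-7% and keeps 96% of the spectrum. The cost is a sentence or two of text and a second preprocessing branch to run and document. No new data are needed, and the Participants section says recruitment had not begun at submission.

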##### Task-state PE signal analysis

BOLD signal analysis of ROIs during the task will be performed using SPM12 (https://www.fil.ion.ucl.ac.uk/spm/software/spm12/). The PE and relative partial differential calculations in the action selection phase and the reward outcome phase will be included as regressors in the general linear model, with ω (see Equation 1) as a covariate (30). The standard hemodynamic function will be constructed for ROIs using MarsBaR (https://sourceforge.net/projects/marsbar/) with FDR correction for control of false discovery rate in voxelwise tests (41). The ROIs will be made with WFU_PickAtlas software (https://www.nitrc.org/projects/wfu_pickatlas) according to the activation map during MDT for PEs.

The ROIs within CEN/SN will be mapped to CEN and SN which are functionally defined according to 14 intrinsic connectivity networks (ICNs) that are comprised of 90 distinct ROIs (42, 43). The DMN, SN, and CEN will be constructed from network templates with the Group ICA of fMRI Toolbox (GIFT, http://mialab.mrn.org/software/gift/) for use in the constrained ICA. The differential functional image (CEN - SN strength) during the first session will be used to create individualized network masks as neurofeedback target regions during the subsequent sessions. The nuisance regressors including six motion parameters and temporal derivatives as well as their quadratic terms and 25 physiological noise components will be taken into consideration. The first two runs of the first session will be discarded without additional analysis. The time courses (extracted using Turbo-BrainVoyager online) of ROIs will be high-pass filtered (0.01 Hz/100 s) and normalized (z-transformed).

##### Self-regulation performance

For each subject in the patient group in each session, self-regulation performance will be assessed with the CEN-SN activation difference (computed through online time courses of ROIs extracted using Turbo-BrainVoyager) during the training. Self-regulation performance will be defined as the mean % signal change of ROIs (CEN and SN) over all the NF runs. The self-regulation performance will then be submitted to an ANOVA with the factors group (NF vs. YC) and session (four sessions) for the group and/or time effects of rt-fMRI NF training.

Additionally, to investigate the pre- and post-training difference in CEN-SN functional connectivity for each patient group, we will apply the paired *t*-tests or Wilcoxon signed-rank tests (depending on parametric or non-parametric distributions) between the pre- and post-training tests, while undergoing MDT behavioral task during neuroimaging.

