#### Real-time fMRI neurofeedback of individual goal-directed system in anhedonic depression

The anhedonic depressed participants (*n* = 40) will be randomized into the neurofeedback (NF) group (*n* = 20) and the yoke control (YC) group (*n* = 20). We used blocked randomization to form the allocation list (1:1 ratio) for the two comparison groups (NF and YC), by using a computer random number generator to select random permuted blocks (size = 10). The NF group will receive rt-fMRI neurofeedback intervention, with ~60 min per session, once per week for a total of four sessions. Participants in the YC group who are paired with one specific participant from the NF group will receive feedback signals from that participant during the same run. Thus, for the YC group, the sham rt-fMRI signals will not be corresponding to the participant's brain activity. The healthy control (HC) group (*n* = 20) will receive no intervention.

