##### Sample size

The sample size is determined based on a heuristic justification (36) according to median recruits (*n* = 18) of fMRI neurofeedback (37). Moreover, given that this is a feasibility study with constraints on limited resources, a power calculation is not necessary according to the reporting and experimental design consensus in the NF field (38).

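### Depending on how it is fitted, the group-by-session ANOVA of self-regulation either excludes patients with a missed session or ignores within-patient correlation; a mixed model avoids both

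*Protocol article*

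**What the plan says.** The section Self-regulation performance sets the unit of measurement: "For each subject in the patient group in each session, self-regulation performance will be assessed with the CEN-SN activation difference". It then gives the score: "Self-regulation performance will be defined as the mean % signal change of ROIs (CEN and SN) over all the NF runs". Read with the session factor that follows, this is one value per patient per session. The test is: "The self-regulation performance will then be submitted to an ANOVA with the factors group (NF vs. YC) and session (four sessions").

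The section on real-time fMRI neurofeedback in anhedonic depression randomises 40 patients, 20 to NF and 20 to YC, and schedules training "with ~60 min per session, once per week for a total of four sessions". The Sample size section gives a heuristic number and no power calculation, "given that this is a feasibility study with constraints on limited resources".

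For this ANOVA the article does not use the term repeated-measures, does not mention complete cases, names no software and states no expected rate of missed sessions. SPSS 22 is named under Behavioral data and for the mediation analysis. A mixed model is named only for choice behaviour. The HAMD-17 and SHAPS comparisons use a separate Bayesian ANCOVA.

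**The concern.** The four session scores from one patient are correlated, and some patients may not have all four. A group-by-session ANOVA with only those two named factors does not deal with both facts at once.

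- **One row per patient, four session columns (classical repeated measures).** The correlation is handled, but a patient with three usable sessions and one empty cell leaves the analysis altogether.
- **One row per patient-session, two factors.** Partial attenders stay, but the model has no patient term, so repeated scores count as independent observations.
- **Keeping partial attenders and respecting the correlation** needs a patient effect, which the article does not state.

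This matters because the abstract asks whether regulating the CEN/SN differential signal is feasible, and this ANOVA is the only between-arm test of regulation that the article describes. If patients who regulate poorly are also those who stop, a complete-case fit compares a selected subset of the randomised arms. With 20 per arm, a few exclusions are a noticeable share.

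**Working it through.** The plan states no analysable number or attendance rate for this test, so there is no figure of its own to reproduce.

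**Inputs from the article:** 40 randomised patients (20 + 20) and 4 sessions, so 40 × 4 = 160 planned patient-sessions.

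**Assumption, not from the article:** each session is missed independently with probability q.

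**Step 1. Loss under the classical repeated-measures fit.** The share of patients with at least one missed session is 1 − (1 − q)^4.

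| q (assumed) | 1 − (1 − q)^4 | Patients excluded of 40 | Session values that exist |
|---|---|---|---|
| 3% | 1 − 0.97^4 = 0.115 | 4.6 | 97% |
| 5% | 1 − 0.95^4 = 0.185 | 7.4 | 95% |
| 10% | 1 − 0.90^4 = 0.344 | 13.8 | 90% |

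At q = 5%, 160 × 0.95 = 152 sessions are observed. Complete cases hold 160 × 0.8145 = 130.3 of them, so about 21.7 observed sessions are discarded. At q = 10% the figure is 144 − 105.0 = 39.0.

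**Step 2. How far this depends on independence.** Misses that cluster in the same patients remove fewer patients. At q = 5% there are 160 × 0.05 = 8 missed sessions; if they fell two to a patient, 8 / 2 = 4 patients would be excluded, not 7.4. If the assumption is instead the share of patients missing any session, 5%, 10% and 20% leave 38, 36 and 32 of 40. With full attendance the loss is zero.

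**Step 3. The long-format two-factor fit.** In one simulated dataset with dropout, this fit kept all 149 observed rows, against 140 for complete cases, so it does not delete. Its fault is the error term. With patient variance σu², residual variance σe² and correlation ρ = σu² / (σu² + σe²), the true variance of an arm mean over four sessions is (σu² + σe²/4)/20, while the fit uses about (σu² + σe²)/80. The ratio is (4σu² + σe²)/(σu² + σe²) = 1 + 3ρ. It is 1 at ρ = 0. At an assumed ρ = 0.49/(0.49 + 0.49) = 0.5 (both SDs 0.7, as in step 4) it is 2.5, so the standard error for the group effect is too small by √2.5 = 1.58. The session and interaction tests err the other way: their error variance is too large, because between-patient variance is left in it.

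**Step 4. Can selective stopping bias the contrast?** An illustrative simulation used 300 replicates, 20 patients per arm, patient and residual SDs of 0.7, and an NF gain of 0.2 per session. The true mean group difference is therefore 0.2 × (0 + 1 + 2 + 3)/4 = 0.30 and the true slope difference 0.20. NF patients stopped with probability 0.3 after any score below −0.3; YC patients never stopped.

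| | Patients used | Mean NF − YC difference | Slope difference |
|---|---|---|---|
| Truth | | 0.30 | 0.20 |
| Complete cases | about 35 of 40 | 0.48 | 0.18 |
| Mixed model, all observed sessions | 40 of 40 | 0.29 | 0.20 |

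Under these chosen settings the mean difference was inflated and the slope difference was slightly reduced. Bias is possible, and its direction depends on the effect examined and on who stops.

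**The case against.** The strongest reply is that the article never says patients with a missed session are removed. That is correct. A reader might infer that the plan requires all four sessions and reports learning in full attenders only. The text does not support that: deletion follows from one way of fitting the ANOVA, and a long-format fit keeps every observed row. Nor does SPSS force deletion. It is not named for this test, and it also offers a mixed-model procedure.

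A second reply is that rules for missed sessions belong in a statistical analysis plan or full protocol, neither of which is shown; the article also points to a preregistration. This disposes of any complaint that a rule is absent. It does not answer the point about the model that is named: either plain reading has a fault, and a better model tests the same effects.

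A third reply is that the size is all assumption. This stands. The article gives no attendance figure, and nothing in it shows that missed sessions are likely.

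Two further inferences should be resisted. One is that the feasibility answer will be too favourable. That needs stopping to be related to regulation success in a particular way, and even when this was built into the simulation the slope difference moved in the unfavourable direction. The other is that yoking multiplies the loss because a donor's missed session cancels the partner's. The article says that YC patients receive a paired NF patient's signal from the same run, but not what happens when that session is missing.

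**Conclusion.** The point holds in conditional form. The stated ANOVA excludes patients with a missed session if fitted as classical repeated measures, and misstates the error variance if fitted as a plain two-factor model on all rows. Under the first fit the loss would be about 11%, 19% or 34% of the 40 patients at assumed independent per-session miss rates of 3%, 5% or 10%, less with clustered misses and nil with full attendance. Under the second, the group-effect variance is understated by 1 + 3ρ, with ρ unknown. Bias in the NF-YC contrast is possible if stopping is related to regulation success, but its direction is not established. This is a low-cost improvement to the regulation (feasibility) analysis, not a demonstrated error in the efficacy comparison.

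**What to change.** Replace the ANOVA with a linear mixed model for session-level self-regulation performance: fixed effects for group, session and group × session, a random patient effect, and all observed sessions from every randomised patient with at least one session. Report the number attending each session by arm beside the result.

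The effects tested are the same as in the present plan. The change is one sentence of analysis wording, with no extra patients, visits or data. It relies on missingness being explained by the scores already observed; if stopping depends on performance that was never recorded, the model does not remove that bias, which is why attendance by arm should be shown.

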Additionally, the current study takes into account the potential confounding factors of motivation and demand characteristics. The mechanism underlying NF may come from NF-specific or non-specific contextual factors as well as general non-specific effects such as practice, placebo, and natural change (cognitive development or decline)(38). Therefore, a double-blind yoke-controlled design is adopted in this study to control for individual differences in motivation and effort. As a limitation, insufficient power may result from the limited sample size. To control for inter-subject variance, yoke-controlled NF will be provided for the participants to modulate the fMRI signals, in which sham feedback has been shown to regulate neural activity in cognitive control compared to passively viewing conditions (52).

The caveat of this study is the use of CEN and SN based on intermittent, rather than continuous imaging feedback signals, due to the signal calculation speed of network parameters and the high cognitive load of momentary feedback (53). Accumulating evidence indicates that intermittent feedback is more efficient than continuous feedback to reinforce the participants' internal thoughts (54, 55). However, other studies showed that continuous feedback improved regulation ability (56). Additionally, monetary reward elicits a greater extent of self-regulation than non-reward feedback (57). Therefore, further study would be able to determine the influence of intermittent vs. continuous feedback and trial-by-trial virtual monetary reward on GD-RL, though the monetary reward in this study is not contingent on participants' decision as in the Markov decision (MD) task. Feedback design for NF training should be carefully considered in future research.

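### The self-regulation ANOVA lists a session effect pooled over NF and sham as an effect of NF training and does not name the group-by-session interaction

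*Protocol article*

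**What the plan says.** Under Self-regulation performance, the protocol article defines the outcome for each patient and session: "Self-regulation performance will be defined as the mean % signal change of ROIs (CEN and SN) over all the NF runs". These values then go into an "ANOVA with the factors group (NF vs. YC) and session (four sessions) for the group and/or time effects of rt-fMRI NF training". No interaction is named for this outcome there or elsewhere in the article.

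The section on real-time fMRI neurofeedback gives the design: 40 patients randomised 1:1 to NF (20) or YC (20), with sessions "once per week for a total of four sessions". Each YC patient sees the feedback of a paired NF patient, so "for the YC group, the sham rt-fMRI signals will not be corresponding to the participant's brain activity".

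The Discussion explains what the control is for. Among the possible sources of change after neurofeedback it lists "general non-specific effects such as practice, placebo, and natural change". It also states that "sham feedback has been shown to regulate neural activity in cognitive control compared to passively viewing conditions".

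For the behavioural task, by contrast, the Statistical analysis section names each interaction with group that will be interpreted.

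**The concern.** A group-by-session ANOVA gives three tests, and they answer different questions.

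- **Group:** do NF and YC differ in performance averaged over the four sessions? This is a valid randomised contrast.
- **Session:** does performance change over sessions, averaged over both arms?
- **Group by session:** does the change over sessions differ between the arms?

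Only the first and third separate real from sham feedback. Half of the patients behind the session effect receive feedback unrelated to their own brain activity. A change common to both arms is exactly what the yoked control was introduced to remove, and the article itself expects that sham feedback may alter neural activity. Yet the wording lists time alongside group as an effect of NF training, joined by and/or, and leaves out the interaction.

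A session effect without learning is also plausible for a technical reason. Under Task-state PE signal analysis, first-session images define the individual masks used in later sessions, and the first two runs of the first session are discarded. The first session therefore differs from the others in both arms.

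At stake is the statement that patients learned to control the CEN-SN signal. If a shared change were reported as successful training, later readings of the clinical and mediation results would start from a wrong premise about target engagement.

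**Working it through.** The article states no alpha, SD, correlation or expected gain for this ANOVA, so there is no figure to reproduce. The calculation shows how the three tests behave under stated assumptions.

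**From the article:** 20 per arm, 40 in total; 4 sessions; factors group (2) and session (4).

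**Assumed:** two-sided 5% level; SD 1 at each session; equal correlation r between sessions, 0.3 to 0.7; a linear rise of d SD from session 1 to session 4, identical in both arms, so no NF-specific learning.

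**Session main effect.** The degrees of freedom are 3 and 38 × 3 = 114. The noncentrality is

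λ = N · d² · Σ(t − 0.5)² / (1 − r), with t = 0, 1/3, 2/3, 1.

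The sum is 0.25 + 0.0278 + 0.0278 + 0.25 = 0.556. For d = 0.5 and r = 0.5, λ = 40 × 0.25 × 0.556 / 0.5 = 11.1. With a critical F of 2.68, this gives a significant session effect in 79% of trials.

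**Group or session.** The group test has a 5% rate here, so the chance of at least one significant main effect is 1 − (1 − 0.79) × 0.95 ≈ 80%.

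**Interaction.** The arms change identically, so its noncentrality is 0 and its rate is 5%.

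| Shared rise d | r | λ (session) | Session | Group or session | Interaction |
|---|---|---|---|---|---|
| 0.3 | 0.3 | 2.9 | 25% | 29% | 5% |
| 0.3 | 0.5 | 4.0 | 35% | 38% | 5% |
| 0.3 | 0.7 | 6.7 | 55% | 57% | 5% |
| 0.5 | 0.3 | 7.9 | 63% | 65% | 5% |
| 0.5 | 0.5 | 11.1 | 79% | 80% | 5% |
| 0.5 | 0.7 | 18.5 | 96% | 96% | 5% |

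Simulation with 4,000 trials per setting agrees: for d = 0.5, a group or session effect in 64%, 80% and 96% of trials, and the interaction in 4.6% to 6.0%.

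**No change in either arm.** If either main effect counted, the rate would be 1 − 0.95² = 9.75% (simulated 9.7% to 10.6%).

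**What the interaction can detect.** Suppose only the NF arm gains, by 0.8 SD. Each arm then departs from the common trend by 0.4 SD, so λ = 40 × 0.4² × 0.556 / (1 − r), which is 5.1, 7.1 and 11.9 for r = 0.3, 0.5 and 0.7. The power is 43%, 58% and 82% (simulated 44%, 58% and 83%). For an NF-only gain of 0.5 SD the simulated power is 19%, 24% and 39%.

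**The case against.** **No decision rule is written.** The article does not say that a session effect alone will be accepted as NF learning. A reader might infer such a rule from and/or, but the text permits that reading without fixing it. The phrase may be loose shorthand for the effects of a two-factor ANOVA, and software normally fits the interaction by default. This stands, and it limits the point to what the wording allows.

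**The percentages are partly built in.** The 80% is the power of a session test to find a session effect that was assumed. It is correct detection of a change over time, and becomes an error only when that change is attributed to NF. This stands too.

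**The article warns about non-specific effects.** The Discussion asks that they be considered when results are explained. That is a general caution. It names no test and does not alter what the analysis section lists as effects of training.

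**Other documents may be more specific.** The Procedure section points to a preregistration and a CRED-NF checklist that are not shown. They may name the contrast. The article nevertheless states which effects it looks for, and that statement is what needs correcting.

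**The interaction is not the only useful test.** A reader might infer that the group main effect is also invalid, or that a one-degree-of-freedom linear trend must be the single test. Neither follows. The group effect is a randomised comparison. With five NF runs per session, learning could occur within the first session and then plateau, and the group effect could show this where a trend would not. The first session is also a poor anchor for a trend, given its different run selection and its role in defining the masks.

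**The outcome is mechanistic.** A reader might infer that the trial's efficacy conclusion is at risk. The analyses of HAMD-17 and SHAPS under Intervention effect analysis compare NF with YC directly, with baseline adjustment, and are unaffected. A transfer run without feedback is also planned to test generalisation, although its analysis is not detailed.

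**Conclusion.** The point holds as one of wording and attribution. The plan lists a session effect pooled over real and sham feedback as an effect of NF training, and it leaves unnamed the interaction that would show different learning in the two arms. A change shared by both arms could therefore be reported as an NF effect.

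The size depends on the assumed gain and correlation, neither of which is in the article; a shared rise of 0.3 SD gives 29% to 57% instead of 65% to 96%. That the session test cannot separate NF from sham does not depend on those assumptions. It is worth correcting because the article reports that recruitment had not begun at submission, and choosing the deciding contrast after the data are seen would be post hoc.

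**What to change.** In the Self-regulation performance section, state that:

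1. evidence of NF-specific self-regulation must come from a between-arm contrast;
2. the group-by-session interaction is the test of differential learning across sessions;
3. the group main effect is kept as the randomised NF-versus-YC contrast of average performance;
4. the session main effect is descriptive and is not evidence of an NF effect.

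A linear-trend contrast between arms may be added but is optional.

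The data and the ANOVA stay the same, and the change takes a sentence or two. The cost is power. Where the arms share part of the change, the interaction is significant less often than the session effect. If only NF patients gain, the two tests have about the same power, but it is modest with 20 per arm: roughly 43% to 83% for a gain of 0.8 SD. A claim of learning will therefore be harder to make, and a non-significant interaction should not be read as proof that no learning took place.
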